**Fig. 1 Fig1:**
[figure not shown]
The flowchart of BAD-study. BAD: Branch atheromatous disease; CTA: Computed tomography angiography; DSA: Digital subtraction angiography; e-CRF: Electronic case report form; END: Early neurological deterioration; HR-MRI: high-resolution magnetic resonance imaging; MRA: Magnetic resonance angiography; MRI: Magnetic resonance imaging; mRS: Modified Ranking scale; NIHSS: National institute of health stroke scale; pCASL: pseudo-continuous arterial spin labelling; PLATO: Platelet Inhibition and Patient Outcomes; SWI: Susceptibility weighted imaging; VWI: Vessel wall imaging. ^*^ CCA: Common carotid artery; ECG: Electrocardiograph; ICA: Internal carotid artery; VA: Vertebral artery; SubA: Subclavian artery; ^†^ TCD: Transcranial doppler; ^‡^ Drugs include Antiplatelet drugs, lipid-lowering drugs including statins, anticoagulant drugs, antihypertensive drugs, antidiabetics, and other neuroprotective drugs

### Study measurements

#### Clinical data

Data of patients will be collected and reported using the electronic Case Report Form (e-CRF) at baseline and follow-up periods. The quality of data will be monitored dynamically by the central center. Clinical items include demographics, medical history, history of medication, clinical presentations, and treatments in hospital. The blood pressure and intake and output volume within 72 h after enrollment are also recorded. The details is shown in Table 1.

**Table 1 Tab1:** Clinical assessment of BAD-related stroke

Items	Assessment
Demographics	Age, gender
Medications prior to stroke	Antiplatelet drugs, statins, anticoagulant drugs, and tirofiban
Medical history	Stroke, hypertension, diabetes mellitus, dyslipidemia, heart disease, chronic respiratory disease, autoimmune diseases, blood system disorders, and thyroid disorder
Personal history	Smoking, alcohol use, and daily activity
Family history	Cardiovascular and cerebrovascular diseases
Current stroke onset	
Time information	Time of symptom onset, arrival at hospital, and enrollment
Stroke symptom	Types (ischemic stroke or transient ischemic attack [TIA]), and presentation (pure motor hemiparesis, pure sensory, sensorimotor syndrome, and others)
Blood pressure	(1) Arrival at hospital, enrollment, and each follow up; (2) Monitor of blood pressure within 72 h after enrollment (≥ 3 times per day, interval time ≥ 2 h)
Heart rate	Arrival at hospital, enrollment, and each follow up
Intake and output volume	Monitor of intake and output volume within 72 h after enrollment
Stroke severity	National Institutes of Health Stroke Scale
Functional assessment	mRS
Activities of daily living	Barthel index
Reperfusion therapy	Data of intravenous thrombolysis, and change of NIHSS score
Medications after stroke	Antiplatelet drugs, lipid-lowering drugs including statins, anticoagulant drugs, antihypertensive drugs, antidiabetics, and other neuroprotective drugs
END	Therapies for END, and time of END occurrence
Use of tirofiban	Time, dosage, duration and side effects

*END* Early neurological deterioration, *TIA* Transient ischemic attack, *mRS* Modified Ranking scale, *NIHSS* National institute of health stroke scale

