### Procedures

The board of primary investigator, neurologists, radiologists, epidemiologists, pharmacologist and statisticians was established on June 1, 2021. All hospital personnel have been trained on the reading of neuroimages in screening stage, the collection of data at baseline and each follow ups, and etc. The enrollment of first case in each center will be confirmed by the board. Eligible patients will be recruited at the time of signing the informed content. Baseline data included demographic and clinical assessments, neuroimages and laboratory data (first ones after stroke onset). Follow-ups will be conducted at 7 days, 30 days, 90 days, 6 months, and 12 months after enrollment, via face-to-face interviews or telephone, when the mRS, cerebrovascular events, adverse effects of medications, and etc. will be evaluated. At the follow-up of 7 days, the event of END will be assessed since stroke onset. The 90-day follow-up is required to be assessed by the neurologists, who are blinded to the clinical, radiological characteristics and treatment of selected patients. The flowchart of BAD-study is shown in Fig. 1.

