### Outcome measures

The primary outcome in our study is the score on the modified Rankin scale at 90 days, which is a 7-point scale ranging from 0 (no symptoms) to 6 (death) [36]. Secondary outcomes include END within 7 days, and NIHSS score, Barthel index, cerebrovascular events (myocardial infarction, new-onset ischemic stroke, new-onset intracranial hemorrhage), and major bleeding complications measured by PLATO (Platelet Inhibition and Patient Outcomes) definition during 90-day follow-up [37]. All-cause mortality within 90 days is also recorded. The follow up times are extended to 1 year, as the long-term outcome of BAD-related stroke remains inconclusive [4, 6].

The END is defined as: 1) From symptom onset to 7 days after enrollment; and 2) Occurrence of deterioration of neurologic deficits after initial assessment: A. An increase of the NIHSS score ≥ 4 points or the NIHSS motor score ≥ 1 point for ischemic patients; or B. The stereotyped attacks still repeat ≥ 3 times after arrival at hospital or progress to persistence status for patients with internal capsule warning syndrome or pontine warning syndrome [12, 38].

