### Statistical analysis

Categorical variables will be presented as frequencies and percentages, such as gender, vascular risk factors, lesions of penetrating artery, and therapies. Continuous variables with non-normal distributions will be shown as median and interquartile range (IQR), while continuous variables with normal distributions as mean and 95% confidence interval (CI), such as age, NIHSS score, blood pressure, and hemoglobin concentration. For the statistical significance analysis of the outcomes, Pearson χ 2 or Fisher’s exact test, Wilcoxon tests, and t-tests will be used, where appropriate, with statistical uncertainty expressed by means of 95% CI. Cox proportional hazards model, Logistic regression model, and Poisson regression model will be used to assess the association between outcomes and clinical or radiological predictors, where appropriate. The good prognosis is defined as 0–2 mRS score, and poor prognosis as 3–6 mRS score at 90 days. Predictors including clinical and radiological features and different treatments will be evaluated. All analysis will be performed using SAS 9.4 and two-sided *P* < 0.05 is considered significant.

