### Current status

The first patient of BAD-study was enrolled on August 16, 2021, after thorough assessment by the board. Until March 13, 2022, our ongoing study has recruited 143 patients. The brief demographic and clinical data of eligible patients are shown in Table3.

**Table 3 Tab3:** Baseline characteristics of patients enrolled in BAD-study

Characteristic	Total
Overall, no.	143
Age, years, mean (95%CI)	59.6 (25.9–93.3)
Female sex, no. (%)	44 (30.8)
Types of stroke onset, no. (%)	
Ischemic Stroke	140 (97.9)
TIA	2 (2.1)
History of stroke, no. (%)	35 (24.5)
Ischemic stroke	33 (23.1)
TIA	1 (0.7)
Cerebral hemorrhage	1 (0.7)
History of hypertension, no. (%)	82 (57.3)
History of diabetes mellitus, no. (%)	44 (30.8)
Elevated LDL-C (Self-report), no. (%)	3 (2.1)
Smoking, no. (%)	
Never	78 (54.5)
Ever	65 (45.5)
Regular drinking, no. (%)	
Never	100 (69.9)
Ever	43 (30.1)
NIHSS score at enrollment, median (IQR)	3 (2–6.3)
Hours from symptom onset to enrollment, median (IQR)	48 (30–65)

*CI* Confidence interval, *IQR* Interquartile range, *TIA* Transient ischemic attack, *NIHSS* National institute of health stroke scale

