## Discussion

BAD-study will be the first prospective clinical-radiological cohort with long-term follow-up and large sample, focusing on the BAD-related stroke, a neglected but clinically meaning subtype of stroke in Asians with poor collateral circulation and high disability [4, 10, 40]. The demographic clinical, radiological, and prognostic characteristics of BAD-related stroke in China will be reported.

In addition, we noticed that the BAD-related stroke was categorized as “stroke of undetermined etiology” in TOAST classification system, and thus failed to reflect its underlying stroke mechanism [4, 6, 40]. Our study will update the original TOAST classification, and prove the concept of BAD-related stroke. In addition, we noticed the higher frequency of cardiogenic embolism in elderly patients with lacunar infarcts, and excluded patients with cardiogenic stroke in our study [41].

With the documented data of laboratory tests, the role of inflammatory indicators on the prognosis of stroke will be assessed. The management of inflammatory indicators might be a novel therapy on reducing END and improving the outcome of BAD-related stroke [12, 28, 29, 31].

With the aid of MRI, MRA, HR-MRI, and ASL, BAD-study will analyze the cerebral artery, vessel wall of parent artery and penetrating artery, artery plaques, brain tissue, cerebral perfusion, and volume of lesion in BAD-related stroke. In addition, visualized analysis of LSA, and its association with outcomes will help neurologists understand the vascular mechanism of END [35, 42]. Radiological data of artery and lesion will provide clues for possible effective drugs. Moreover, quantitative analysis will be conducted to analyze the effect of lesion on the volume of gray matter and white matter, as global brain inflammation could be elicited by localized lesion [43, 44]

Besides, the comparison of different therapy strategies on primary outcome and END will provide direct clinical evidence to optimize the acute therapy in BAD-related stroke [13] and find the probably effective strategy of preventing END [12]. Based on the results of BAD-study, a risk prediction model will be generated for the prognosis, which may help neurologists individualize treatment strategy.

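### Treatments begun after, or because of, early neurological deterioration (END) can enter the analysis as predictors of it, since the stated predictor pool and END window impose no time order

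*Protocol article*

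**What the plan says.** **Outcome window.** The Outcome measures section defines END as deterioration "From symptom onset to 7 days after enrollment", occurring after an initial assessment. The Procedures section adds: "At the follow-up of 7 days, the event of END will be assessed since stroke onset". Deterioration before enrolment can therefore count.

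**What is recorded inside that window.** Table 1 (Clinical data) lists drugs given after the stroke, the timing, dosage and duration of tirofiban, the treatments given for END, and the time at which END occurred. The text above the table states: "The blood pressure and intake and output volume within 72 h after enrollment are also recorded". The table repeats this for fluids: "Monitor of intake and output volume within 72 h after enrollment".

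**What is analysed.** The Statistical analysis section relates outcomes to clinical or radiological predictors by Cox, logistic or Poisson models and adds: "Predictors including clinical and radiological features and different treatments will be evaluated". It also defines good and poor prognosis by the 90-day modified Rankin Scale (mRS).

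**Intended use.** The Discussion presents the comparison of therapies on the primary outcome and END as evidence for optimising acute treatment. It says that "a risk prediction model will be generated for the prognosis, which may help neurologists individualize treatment strategy".

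**The concern.** END is an outcome, treatments are named predictors, and a therapy comparison on END is announced. Nothing in the article requires the treatment to come first. Clinicians react to deterioration by changing treatment, and the case report form captures those reactions. If drugs are coded as given or not given in hospital, a drug used as a response to END will be over-represented among END patients and will look as if it caused END.

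The stake is the treatment evidence. Study objective 4 and the end of the Discussion say that the tirofiban data will support later randomised trials. A reversed association with END would pass straight into that planning.

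The 72 h blood pressure and intake/output series would have the same fault if summarised over the full 72 h and related to END, because part of the summary would be measured after the event.

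**Working it through.** The plan gives no figure on this point to reproduce. The check is one of timing, followed by an illustration of size.

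**1. Windows.** Inputs: END runs to 7 days after enrolment, 7 × 24 = 168 h (Outcome measures). Onset to enrolment has median 48 h, IQR 30 to 65 h, in 143 patients (Table 3). Monitoring covers the 72 h after enrolment (Table 1). With t the hours from onset to enrolment:

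| t (h) | END window, t + 168 | before enrolment, t/(t + 168) | monitoring, 72/(t + 168) | elapsed when monitoring ends, (t + 72)/(t + 168) |
|---|---|---|---|---|
| 30 | 198 h | 15% | 36% | 52% |
| 48 | 216 h | 22% | 33% | 56% |
| 65 | 233 h | 28% | 31% | 59% |

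At the median, monitoring covers hours 48 to 120 of a 216 h window. Even if END counted only from enrolment, the 72 h would still lie wholly inside it (72/168 = 43%). These are shares of time, not of events, because the article gives no distribution of END times. The pre-enrolment share is an upper limit, because END also requires an initial assessment whose time is not summarised.

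**2. Treatment and END.** Assume that the drug has no effect, that a share b = 0.15 of all patients receive it regardless of END, and that a share r of the remaining END patients start it after END. Then:

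- uptake without END = b, odds 0.15/0.85 = 0.176
- uptake with END = 1 − (1 − b)(1 − r)
- spurious odds ratio = odds with END / odds without END

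| r | uptake with END | odds | odds ratio |
|---|---|---|---|
| 0.10 | 1 − 0.85 × 0.90 = 0.235 | 0.307 | 1.74 |
| 0.30 | 1 − 0.85 × 0.70 = 0.405 | 0.681 | 3.86 |
| 0.50 | 1 − 0.85 × 0.50 = 0.575 | 1.353 | 7.67 |

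The odds ratio depends on b and r only, so no END rate need be assumed. Neither b nor r is in the article.

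**3. Blood pressure, as an illustration only.** Cohorts of 450 were simulated with no true effect: END 20%; 70% or 90% of END in the first 72 h after enrolment and the rest by 168 h; baseline pressure with mean 150 and SD 15 mmHg; and a logistic model of END on the 72 h mean. A shift after END of 5 mmHg gave P < 0.05 in 15–27% of 600 cohorts per setting, 10 mmHg in 50–72%, and 15 mmHg in 81–96%. A separate run with no shift gave 3–7%, as it should at a nominal 5%. The END rate, END timing, mean, SD and shift are all assumptions.

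**The case against.** The best counter-argument is that this is an omission. Covariate timing, landmarks and time-updated covariates are commonly left to a full protocol or analysis plan, which is not shown. Cox models are named where appropriate and can take time-dependent covariates. The times of END and of tirofiban are collected, and treatments given for END are a separate item. Nothing prescribes a wrongly ordered analysis. This limits the point without removing it: the article itself fixes the predictor pool, the END window and the therapy comparison on END, and together these admit exposures that follow the outcome.

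Three stronger readings are tempting, and the objection defeats them:

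- A reader might infer that the 72 h pressure and fluid series is a planned predictor of END. The article says only that it is recorded. Its inclusion could be drawn only from the broad reference to clinical features, and a 72 h mean is mentioned nowhere.
- A reader might infer that the risk model depends on data not yet known when treatment is chosen. Its inputs and prediction time are not listed, and it could be built from baseline data.
- A reader might infer that 72 h values also run backwards for prognosis. Prognosis is defined by 90-day mRS, which those values precede, although they may lie downstream of END.

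It is also fair to say that the vascular-mechanism objective is pursued mainly through vessel-wall and plaque imaging, so it does not rest on pressure or fluid data.

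**Conclusion.** The point holds for treatments and END. Under the stated plan, a drug started after or because of END can be analysed as a predictor of END and appear to cause it. The spurious odds ratio is 1.74 to 7.67 for 10% to 50% extra uptake after END, given 15% uptake otherwise and no true effect. Those uptake figures are assumed, so the range shows how large the bias could be and does not estimate it.

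For the 72 h series the point is conditional: it lies inside the END window and would carry the same reversal if used as an END predictor. The simulation shows that modest shifts could matter, but it rests entirely on assumed inputs. For the prognostic model, the defect is that neither prediction time nor eligible inputs are stated, while the intended use is to guide treatment. The sample size is not affected.

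**What to change.** Add two rules to the Statistical analysis section.

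**(a) END analyses.** A treatment or measurement counts only if it precedes END. It enters either as a time-updated covariate in a Cox model, or as its value at a landmark in patients still END-free at that time. The recorded times of END and of tirofiban are used. Treatments given for END are not exposures for END. Patients whose END precedes enrolment are left out of analyses that use enrolment or later values. The full 72 h summary of pressure or fluids may be used for 90-day mRS only.

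Merely deleting drugs started after END from an ever/never comparison would not be enough. END-free patients would still have the whole window in which to start the drug, which biases the comparison the other way.

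**(b) Prognostic model.** State a fixed prediction time, chosen so that the baseline imaging is available, and restrict candidate predictors to items known by then.

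**Cost.** No change to sample size, and no new collection for END or tirofiban times. END analyses lose some events, and apparent discrimination may fall. The article does not say that clock times are kept for every drug or reading: Table 1 gives a minimum frequency and spacing for blood pressure and no timing for individual fluid records. Items without a recorded time cannot enter the time-updated analysis.

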#### Laboratory tests

According to Chinese guidelines and clinical practice [34], initial clinical biochemistry routine tests including total blood cell count, liver and renal functions, lipid levels, and blood coagulation test will be recorded under standard lab procedures. If applicable, autoimmune biomarkers, homocysteine concentrations, glycosylated hemoglobin, fasting glucose, thyroid gland function, high sensitivity C reactive protein, Protein C, Protein S, Antithrombin III, and activated protein C will be measured at baseline. If applicable, lipid levels will be measured at 90-day follow up.

### Imaging protocols

#### MRI

The MRI studies are conducted on 3 T MR scanners (GE Discovery 750 or SIEMENS Vida). Three dimensional (3D) T1, MRA, high-resolution vessel wall imaging and pseudo-continuous arterial spin labelling (ASL) are conducted, and the parameters are shown in Table 2. Based on Table 2, the imaging parameters are modified and verified at each center, if applicable. In addition, routine T1-weighted, T2-weighted, fluid-attenuated inversion recovery (FLAIR), diffusion-weighted imaging, apparent diffusion coefficient (ADC) and susceptibility weighted imaging (SWI)/T2*WI will also be performed, using the standardized protocol in each center.

**Table 2 Tab2:** MRI parameters of vascular imaging

Scanner	Sequences	TR/TI/TE (ms)	FOV (mm)	Matrix	FA	Number of slices	Slice thickness (mm)	LD/PLD (ms)	Time
SIEMENS	T1-SPACE	900/-/14	170 × 170	288 × 288	-	240	0.6	-	8 min 56 s
	3D-T1 (MPRAGE)	2300/900/3.5	256 × 232	256 × 232	8	192	1	-	4 min 40 s
	TOF-MRA	20.7/-/3.8	216 × 174	432 × 324	20	216	0.4	-	6 min 20 s
	ASL	4550/-/12	210 × 210	60 × 60	180	36	4	1800/2000	2 min 7 s
GE	T1-CUBE	800/-/15.8	204 × 184	320 × 256	-	248	0.8	-	4 min 45 s
	3D-T1 (Bravo)	6.7/400/2.9	256 × 230	256 × 256	12	170	1.0	-	4 min 11 s
	TOF-MRA	16/-/2.1	220 × 165	352 × 224	20	176	1.2	-	3 min 28 s
	ASL	4886/-/10.5	240 × 240	64 × 64		40	4	1450/2025	4 min 44 s

*ASL* Arterial spin labeling, *FA* Flip angle, *FOV* Field of view, *LD* Labeling duration, *PLD* Post-labeling delay, *TE* Echo time, *TI* Inversion time, *TOF-MRA* Time-of-flight MR angiography, *TR* repetition time

#### Other image techniques

Other assessment techniques for cerebral artery, carotid artery, vertebral artery, and subclavian artery, including MRA, CTA, DSA or vascular ultrasound are conducted according the standardized protocol in each center. In addition, the results of Holter, transcranial doppler sonography, and ultrasonic cardiogram will be recorded based on the criteria at each center, if applicable.

#### Image analysis and classification

The BAD-related stroke will be divided as two groups: 1) Lesion in area of LSA; and 2) Lesion in area of PPA. The plaque, stenosis, vessel wall, and cerebral perfusion of PPA and LSA will be assessed. The vascular lesion sites of penetrating artery and its parent artery are grouped into three types: 1) Plaque within parent artery blocking the branch orifice; 2) Plaque extending into the branch from parent artery; 3) Plaque originating in orifice of branch [3]. The length, thickness, square, volume, and signal of plaque will be measured. In LSA analysis based on 3 T-VWI, the number, length, and shape of LAS will also be evaluated [35].

The process of image collection, storage, synthesis and analysis are guided by a committee including senior radiologists and neurologists. All images will be evaluated by two experienced neurologists and will be reviewed by senior neurologist [name] in case of disagreement.

### Outcome measures

The primary outcome in our study is the score on the modified Rankin scale at 90 days, which is a 7-point scale ranging from 0 (no symptoms) to 6 (death) [36]. Secondary outcomes include END within 7 days, and NIHSS score, Barthel index, cerebrovascular events (myocardial infarction, new-onset ischemic stroke, new-onset intracranial hemorrhage), and major bleeding complications measured by PLATO (Platelet Inhibition and Patient Outcomes) definition during 90-day follow-up [37]. All-cause mortality within 90 days is also recorded. The follow up times are extended to 1 year, as the long-term outcome of BAD-related stroke remains inconclusive [4, 6].

The END is defined as: 1) From symptom onset to 7 days after enrollment; and 2) Occurrence of deterioration of neurologic deficits after initial assessment: A. An increase of the NIHSS score ≥ 4 points or the NIHSS motor score ≥ 1 point for ischemic patients; or B. The stereotyped attacks still repeat ≥ 3 times after arrival at hospital or progress to persistence status for patients with internal capsule warning syndrome or pontine warning syndrome [12, 38].

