Inclusion criteria:1. Age:18–80 years.2. Acute cerebral infarction, if the clinical manifestations are transient, new infarct lesion should be found on Diffusion Weighted Imaging (DWI) at the same time.3. The time from symptom onset to enrollment is less than 72 h. If the onset time was unknown, the time of last known free of new ischemic symptoms to enrollment is less than 72 h.4 Meet all the following radiological criterial:1) DWI lesion: single (isolated) deep (subcortical) infarct;2) The culprit vessels are the LSA or PPA, and the infarct lesion on DWI conforms to one of the following characteristics (A/B):A. LSA: (1) “Comma-like” infarct lesions with “Fan-shaped” extension from bottom to top in the coronary position; OR (2) ≥ 3 layers (layer thickness 5–7 mm) on axial DWI images of the head;B. PPA: the infarct lesion extends from the deep pons to the ventral pons on the axial DWI of the head.3) No ≥ 50% stenosis on the parent artery of the criminal vessel (i.e. corresponding basilar or middle cerebral artery) (confirmed by magnetic resonance angiography [MRA] or computed tomography angiography [CTA] or digital substraction angiography [DSA]).5 Signed informed consent by the patient or legally authorized representatives.Exclusion criteria:1. Intracranial hemorrhagic diseases, vascular malformations, aneurysms, brain abscesses, malignant space occupying lesions or other non-ischemic intracranial lesions observed by baseline head CT and MRI, MRA/CTA/DSA.2. There was ≥ 50% stenosis of extracranial vessels with ipsilateral serial relationship.3. Cardiogenic embolism: atrial fibrillation, myocardial infarction, valvular heart disease, dilated cardiomyopathy, infective endocarditis, atrioventricular block disease, heart rate less than 50 beats /min.4. Have received or plan to receive acute endovascular treatment after onset of the disease.5. Stroke caused by other clear causes, such as moyamoya disease, arterial dissection, vasculitis, etc.6. mRS score prior to the onset of the disease was ≥ 2 points.7. Known malignant tumor.8. Life expectancy ≤ 6 months.9. Contraindications of 3 T MRI examination.10. Pregnant or lactating women.11. Participation in another clinical within 3 months before enrollment, or taking part in another ongoing study.

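### The END window runs from symptom onset to 7 days after enrolment, so its length differs between patients and an unknown share of END can precede enrolment and some exposures

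*Protocol article*

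**What the plan says.** The Outcome measures section gives a short label and then a longer definition. The label is "Secondary outcomes include END within 7 days", with no time origin. The definition sets the window as "From symptom onset to 7 days after enrollment" and adds a second condition, "Occurrence of deterioration of neurologic deficits after initial assessment". The initial assessment is not dated. Criterion A is a rise in total or motor NIHSS. Criterion B, for the warning syndromes, counts from hospital arrival.

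Procedures confirms the early start: "At the follow-up of 7 days, the event of END will be assessed since stroke onset". It also places recruitment at the signing of consent and schedules the visit 7 days after enrolment. The inclusion criteria require that "The time from symptom onset to enrollment is less than 72 h". Table 3 reports an onset-to-enrolment time of 48 h (median; IQR 30–65 h) in the first 143 patients, and gives the NIHSS at enrolment.

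Table 1 includes "Monitor of intake and output volume within 72 h after enrollment", with blood pressure monitored over the same 72 h. It also records the times of onset, arrival and enrolment, the time END occurred, the treatments given for END, and the timing of tirofiban.

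The vascular mechanism of END is the first secondary objective. Statistical analysis relates outcomes to clinical and radiological features and treatments. The Discussion says that therapy strategies will be compared on END.

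**The concern.** There are two problems.

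First, the definition does not match its label. Seven days is the distance from enrolment to the end of the window, but the window opens earlier, by an amount that differs between patients. END incidence then combines events before and after enrolment over unequal periods. The reference NIHSS is also open. If it is the enrolment score, worsening before enrolment cannot register under criterion A, although the window includes it. If it is the arrival score, that worsening counts. The two readings give different END rates.

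Second, if END is counted from onset while an exposure is measured or started later, the exposure may be a consequence of END. A drug given because a patient deteriorated would look harmful. Blood pressure or fluid management changed after deterioration would look like a cause. This bears on the mechanism objective and on the comparison of therapies on END.

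**Working it through.** **Inputs from the article.** Onset-to-enrolment time *t*: 30, 48 and 65 h (Table 3 quartiles) and the 72 h limit (inclusion criteria). Follow-up after enrolment: 7 days = 168 h.

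**Inputs assumed, because the article does not give them.** Time from onset to initial assessment *a*: 0 to 24 h. Timing of END among patients who have it: either even over the window, or exponential from onset with mean *m* = 24, 48 or 72 h, truncated at the end of the window.

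**Step 1: window length from onset, *t* + 168 h.**

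| *t* | Window | Part before enrolment, *t*/(*t* + 168) |
|---|---|---|
| 30 h | 198 h = 8.25 days | 15% |
| 48 h | 216 h = 9.0 days | 22% |
| 65 h | 233 h = 9.7 days | 28% |
| 72 h (limit, not reached) | 240 h = 10 days | 30% |

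The label's 7 days fits only the part after enrolment. The window differs by 65 − 30 = 35 h between the quartiles. This step needs no assumption.

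**Step 2: share of END before enrolment at the median *t* = 48 h.** Only END after the initial assessment counts, so the countable window runs from *a* to 216 h.

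- Even timing: (48 − *a*)/(216 − *a*). With *a* = 0 this is 48/216 = 22%; with *a* = 24 h it is 24/192 = 12.5%.
- Front-loaded timing: [1 − exp(−(48 − *a*)/*m*)] / [1 − exp(−(216 − *a*)/*m*)].

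| Mean *m* | *a* = 0 | *a* = 24 h |
|---|---|---|
| 24 h | 86% | 63% |
| 48 h | 64% | 40% |
| 72 h | 51% | 30% |

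The range is therefore about 12–22% with even timing and about 30–86% with front-loaded timing. Setting *a* = 0 ignores the initial-assessment condition and gives the upper end.

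**Step 3: order of exposures and event.** For a patient enrolled at 48 h, the 72 h of monitoring runs from 48 to 48 + 72 = 120 h after onset.

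| Item | Can it follow END? |
|---|---|
| Demographics, history, prior medication | No |
| Baseline laboratory data (first after onset) | Not tied to enrolment; often earlier |
| Blood pressure at arrival | Taken at arrival, so generally earlier |
| Acute treatment | May start before or after END |
| Monitored blood pressure and fluid balance | Yes: all of it follows an END before enrolment |
| Treatments given for END | Yes, by definition |

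**The case against.** Starting at onset is a defensible choice for a cohort that describes the course of the disease, and the article states it consistently in Procedures and Outcome measures. Counting only from enrolment would lose early deterioration. Table 1 already collects the times needed to put events in order, and records treatments for END separately from other medication. Rules for time-dependent exposure or delayed entry usually sit in an analysis plan or full protocol, neither of which is shown. All of this stands. Nothing here should be read as saying that such rules are missing, or that END before consent must never be counted.

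A reader might go further and infer three things that the article does not support.

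- That many END events precede enrolment. No count or timing of END is reported, and the range above is too wide to settle it.
- That END precedes the predictors and treatments in general. Several predictors are fixed or measured earlier, and treatment can start before both consent and END.
- That monitored blood pressure, fluid balance or enrolment NIHSS will be modelled as predictors of END. They are listed as collected data, enrolment NIHSS appears in Table 3 only as description, and all could properly be related to 90-day mRS.

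The objection does not remove the mismatch between label and window, the unequal window length or the undated reference. These lie in the outcome definition itself. The reverse-causation risk remains too, because END is to be compared across therapies and examined for mechanism under a window that opens before some exposures.

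**Conclusion.** The point holds in limited form. The article's own figures show that the defined window is not 7 days from onset and differs between patients: 8.25 to 9.7 days across the IQR, just under 10 at the limit. The initial assessment has no date.

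That END can precede enrolment and some exposures follows from the definition. How often it does is unknown. The shares of about 12–22% and 30–86% rest on assumed END timing and an assumed first assessment 0–24 h after onset, so they show a plausible range and are not estimates. Reverse causation is a risk if END is analysed as defined without regard to order; it is not an established feature of the planned models.

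This should be fixed, but it does not threaten the study. END is one of several secondary outcomes, and the 90-day mRS primary outcome is unaffected.

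**What to change.** 1. State one time origin, one window length common to all patients, and one reference NIHSS (for example, the first after arrival). Make the outcome label match.
2. Report END before and after enrolment separately, using the recorded times.
3. In predictor, mechanism and treatment analyses of END, count only END that occurs after the exposure was measured or started. Use time-dependent exposure, or delayed entry in Cox models. Exclude treatments given for END from the exposures.

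The cost is a change of wording and some programming, since Table 1 already holds the onset, arrival, enrolment, END and tirofiban times. There are two downsides. Fewer END events remain for the models. The choice of origin is also a trade-off: 7 days from onset would leave only about 168 − 72 = 96 h (4 days) after enrolment for the latest enrolees, while 7 days from enrolment gives everyone 168 h but leaves earlier END to the descriptive report.
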